### **8.3 ENDPOINTS AND EVALUATIONS**

The studied procedure will be considered as safe if:

No severe SAE related to treatment procedure has been documented.

All patients' case profiles will be reviewed by a committee composed by 3 physicians. The main task of this committee will be to evaluate collected data and to give an opinion on treatment safety. The committee will analyze all treatment emergent AE(s) and propose categorization as treatment-related or not. In case of disagreement, majority (2 out of 3) committee's opinion will be considered as final decision.

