#### 8.2.2 **Decision rules for choice of dose regimen**

This study has for objective to assess MTD and MAD in term of MaaT033 activity (bacteria engraftment). Activity assessment requires a minimum of 6 patients to allow for a sufficient robust analysis of engraftment.

Activity and tolerability assessment may depend both on duration of treatment and/or daily dose. Therefore, the study will assess both 7 days and 14 days dose regimen, for the 3 capsules/day dosing.

Therefore, the study will ensure that a minimum of 6 patients is included for all the dose regimen that do not reach the MTD.

Definitions:

**Minimal Active Dose (MAD):** Minimum dose regimen that will lead to a minimal activity (1 or 2, cf chapter 8.3.2) of the product.

|                                                                                   |                    |                                                                      |
|-----------------------------------------------------------------------------------|--------------------|----------------------------------------------------------------------|
| [figure not shown] | DOCUMENT    | Protocol ID : MPOH05
EudraCT N° : 2019-004253-89
Version: 10.0 |
|                                                                                   | CIMON STUDY | Date : 04 MAY 2021
Page 24 / 70                                   |

**Dose Limiting Toxicity (DLT):** Toxicity event will be defined as any related adverse event grade >3 based on CTCAE v5.0 criteria for:

- Blood and lymphatic system disorders (DLT when grade4 or 5)
- Immune system disorders (DLT when grade4 or 5)

And any related adverse event grade  $\geq 3$  for all other system organ.

**Maximal Tolerated Dose (MTD):** Maximal dose for which only 0 or 1 patient do experience limiting toxicity out of a cohort of 6 patients.

The study has an adapted “6 dose titration” escalation design to allow for assessment of tolerability (research of the Maximal Tolerated Dose) and of activity (research of Minimal Active Dose):

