- **1st level of dose for 1st cohort:** - 3 Patients will be treated with one capsule/day on day 1 and D7. The Safety Committee (SC) will evaluate occurrence of Limiting Toxicity after the 3 patients will have completed V3. If no patient experiments a DLT, the following cohort will use dose level 2 *i.e.* 1 capsule/Day for 7 days. If one or more patient experiment a DLT, the SC might consider study stop recommendation or cohort continuation. The purpose of this cohort is to assess feasibility of the whole procedure and check any unexpected tolerability issue that would prohibit continuation of the experimentation. As the dose schedule is not considered as sufficient enough to allow for any effective activity, it will not be considered for the choice of final dose.
- **2nd Level of dose (cohort2):** 6 patients will be treated with 1 capsule/day for 7 days. The Safety Committee (SC) will evaluate occurrence of Limiting Toxicity after the 6 patients will have completed V3. If no or 1 patient experiments a DLT, the following cohort will use dose level 3 *i.e.* 3 capsules/day for 7 days. If two or more patients out of 6 experiment a DLT, the study will be stopped.
- **3rd level of dose (cohort3):** 6 patients will be treated with 3 capsules/day for 7 days. The Safety Committee (SC) will evaluate occurrence of Limiting Toxicity after the 6 patients will have completed V3. If no or 1 patient experiments a DLT, the following cohort will use dose level 4 *i.e.* 3 capsules/D for 14 days and dose level 5 *i.e.* 9 capsules/day for 7 days. If two or more patients out of 6 experiment a DLT, the study will be stopped.
- **4th level of dose:** 6 patients will be treated with 3 capsules/day for 14 days. The Safety Committee (SC) will evaluate occurrence of Limiting Toxicity after the 6 patients will have completed V3. If no or 1 patient experiments a DLT, the following cohort will use dose level 5 *i.e.* 9 capsules/day for 7 days. If two or more patients out of 6 experiment a DLT, the study will be stopped. Of note, if 2 or more DLT are reported during the 7 first days of treatment, then the SC will re-assess cohort3 evaluation.

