- **5th level of dose:** 6 patients will be treated with 9 capsules/day for 7 days. The Safety Committee (SC) will evaluate occurrence of Limiting Toxicity after the 6 patients will have completed V3. If two patients or more experiment a DLT, the study will be stopped and MTD will be considered as dose level 4. If one patient or less experiments a DLT, the MTD will be considered dose level 5.

**In any of the cohort 2 to 5, if any safety signal suggesting potential DLT is reported in 2 or more patient before the end of the inclusion of all patient of the cohort, inclusion of subsequent patient will be suspended and ad hoc meeting of the DSMB will be hold with all available information to assess those potential DLT and decide on the continuation or stopping the study.**

**A 24-hour gap should be respected between inclusions of the first 3 patients of each cohort to consider potential early or delayed toxicities.**

|                                                                                   |                    |                                                                      |
|-----------------------------------------------------------------------------------|--------------------|----------------------------------------------------------------------|
| [figure not shown] | DOCUMENT    | Protocol ID : MPOH05
EudraCT N° : 2019-004253-89
Version: 10.0 |
|                                                                                   | CIMON STUDY | Date : 04 MAY 2021
Page 25 / 70                                   |

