#### **12.1.4.1 Tolerability consideration:**

Investigators will be trained regarding the mode of action of the investigational medicinal product and to be particularly attentive to any signs of toxicity.

**Dose Limiting Toxicity (DLT):** Based on the literature and our preclinical data, no particular toxicity is expected. Toxicity events will be defined as any at least possibly related adverse event grade  $\geq 3$  based on CTCAE v5.0 criteria. Due to the specific therapeutic protocol that blood cancer patients usually follow, the follow-up of patients in term of DLT is set from V1 (end of neutropenia) to V3 (start of a new chemotherapy cycle, or consolidation). Nevertheless, there are some anatomical or physiological system events that will be considered as expected in the context of patients with AML or HR-MSD, and thus not related to the treatment. Such events will only be considered DLT when grade  $> 3$ :

- Blood and lymphatic system disorders (DLT when grade 4 or 5)
- Immune system disorders (DLT when grade 4 or 5)

Depending on the number of DLTs, the dose is either escalated (0 DLTs) or de-escalated ( $\geq 2$  DLTs). Due to our specific drug activity assessment goals, cohorts 2 to 5 will systematically be expanded with 3 extra patients (0 or 1 DLTs) each.

|                                                                                   |                    |                                                                      |
|-----------------------------------------------------------------------------------|--------------------|----------------------------------------------------------------------|
| [figure not shown] | DOCUMENT    | Protocol ID : MPOH05
EudraCT N° : 2019-004253-89
Version: 10.0 |
|                                                                                   | CIMON STUDY | Date : 04 MAY 2021
Page 49 / 70                                   |

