#### **12.1.4.3 Recommended Phase 2 Dose RP2D**

Once the MTD or MED is determined, or once the highest dose has been reached without declaring an MTD, the cohort review committee will select the recommended dose for the following studies with MaaT033 (recommended Phase 2 dose; RP2D).

RP2D usually is the highest dose with a pre - specified DLT rate. In this study, this dose will be the MTD, a dose below the MTD, or any other dose suggested upon clinical evaluation or all available safety, activity and efficacy parameters.

In case an RP2D is selected that is not the MTD, a minimum of 6 patients will need to be treated and followed-up for 7 days at this dose level (with a maximum of 1 DLT observed), before declaring it as the RP2D.

|                                                                                   |                    |                                                                      |
|-----------------------------------------------------------------------------------|--------------------|----------------------------------------------------------------------|
| [figure not shown] | DOCUMENT    | Protocol ID : MPOH05
EudraCT N° : 2019-004253-89
Version: 10.0 |
|                                                                                   | CIMON STUDY | Date : 04 MAY 2021
Page 50 / 70                                   |

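### The only stated criterion for calling the procedure safe is not reconciled with the DLT rule, and sections 8.2.2 and 12.1.4.3 disagree on whether the top dose can be reached without an MTD

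*Protocol*

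**What the plan says.** **Safety criterion.** Section 8.3 opens the endpoint section by saying when the procedure will be considered safe: "No severe SAE related to treatment procedure has been documented". It names no dose level, denominator or window. A three-physician committee then judges relatedness and gives an opinion on safety. Section 14.3.5 leaves the conclusive safety decision to the committee without naming a criterion.

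**DLT rule.** Section 8.2.2 defines the MTD as "Maximal dose for which only 0 or 1 patient do experience limiting toxicity out of a cohort of 6 patients". For levels 2 to 4, "If two or more patients out of 6 experiment a DLT, the study will be stopped", so 0 or 1 of 6 passes. Cohort 1 has three patients and its own rule: "If one or more patient experiment a DLT, the SC might consider study stop recommendation or cohort continuation". Section 12.1.4.1 gives the DLT definition: "Toxicity events will be defined as any at least possibly related adverse event grade" 3 or higher, with grade 4 or 5 required for blood/lymphatic and immune disorders. Seriousness is not part of it, and the window is V1 to V3.

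**Top dose.** For level 5, section 8.2.2 says: "If one patient or less experiments a DLT, the MTD will be considered dose level 5". Section 12.1.4.3, on choosing the RP2D, lists as one possible outcome "or once the highest dose has been reached without declaring an MTD".

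**The concern.** Two stated rules lead to statements about safety, they count different things, and no order of precedence is given. One is a zero-event criterion for the procedure as a whole. The other tolerates one event in six at each of four levels. The word safe has consequences: section 8.3.1 rests the best regimen on the minimal dose that is both safe and active. If a serious DLT occurs at a level that passes, the report could say that the regimen is tolerated and also that the safety criterion was not met. The protocol would not settle which statement stands.

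The second problem is what MTD means. Under 8.2.2 it is the highest level that passes, so level 5 earns the label even with no DLT at all. Under 12.1.4.3 it is possible to reach the top and have no MTD. Two other places also treat the MTD as a limit that is reached. Section 12.1.4.2 calls a review when two or more patients have a DLT, to confirm that the MTD has been reached. Section 8.2.2 itself speaks of regimens that do not reach it. Because 12.1.4.1 expects no particular toxicity, the disputed branch is the likely one. The primary objective is the maximal tolerable dose, so the ambiguity falls on the main result.

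**Working it through.** **Plan's own figure.** Cohort 1 has 3 patients and cohorts 2 to 5 have 6 each: 3 + 4 × 6 = 27, which matches the stated maximum. The protocol gives no operating characteristics for either rule, so there is none to reproduce.

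**Assumptions.** The DLT risk p per patient is the same in all cohorts, and a share s of DLTs are serious. The protocol gives neither, so ranges are shown. Cohort 1 is taken to pass at 0 of 3. Related severe SAEs after V3 are not counted, although section 8.3 sets no window. As a guide to p, the table in section 6.4 shows 1 related SAE in 25 patients (4%) in the earlier AML trial and 1 in 81 (1.2%) overall. Those were mostly other products, all given by enema, and the event's grade is not stated.

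**Formulas.**
- One level passes: c = (1−p)^6 + 6p(1−p)^5
- Full escalation passes: E = (1−p)^3 × c^4
- No event in 27: Z = (1−p)^27
- Passes but 8.3 criterion missed, all DLTs serious: E − Z

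| p | c | E | Z | E − Z |
|---|---|---|---|---|
| 1% | 0.9985 | 0.965 | 0.762 | 0.20 |
| 2% | 0.9943 | 0.920 | 0.580 | 0.34 |
| 5% | 0.9672 | 0.750 | 0.250 | 0.50 |

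**Only some DLTs serious.** Replace c by c0 = (1−p)^6 + 6p(1−s)(1−p)^5, the chance that a level passes with no serious DLT. The chance of conflict is then E − (1−p)^3 × c0^4. At p = 5%:
- s = 50%: 0.750 − 0.450 = 0.30
- s = 25%: 0.750 − 0.586 = 0.16

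**Largest gap allowed by the rules.** With 1 of 6 at each of levels 2 to 5, level 5 is the MTD with 4 DLTs in 27 patients (14.8%, exact 95% CI 4.2% to 33.7%). One serious DLT is enough to miss the 8.3 criterion.

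**Top dose.** At p = 2%, level 5, once opened, passes and is labelled the MTD with probability 0.994. A result of 0 of 6 has an exact 95% upper bound of 1 − 0.025^(1/6) = 45.9%; for 1 of 6 it is 64.1%. A clean level 5 therefore neither locates a toxicity limit nor excludes a substantial DLT risk.

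**The case against.** Several stronger readings are tempting, and the text does not support them.

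- A reader might infer that any single DLT makes the product both tolerated and not safe. It does not. Section 12.1.3.6 separates severe from serious, and a non-serious grade 3 DLT counts under 8.2.2 without touching 8.3.
- A reader might take the 8.3 condition as necessary. Its literal wording is a sufficient condition. That softens the conflict but does not remove it, because no other criterion for safe is stated: after one severe related SAE, the protocol would have no criterion left to apply.
- A reader might infer that one SAE can flip the MTD. It cannot through 8.3, because the MTD follows from the DLT counts in 8.2.2 alone. Overall safety is a secondary objective, decided by a committee.
- A reader might say that naming level 5 the MTD at 0 of 6 breaks the MTD definition. It applies that definition. The mismatch is with 12.1.4.3.
- A reader might take the chance of at least one event in 27 (24%, 42% and 75% at 1%, 2% and 5%) as the chance of conflict. It is larger than that, because it includes trials in which escalation also fails.

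It can also be said that the MTD label has limited effect, since 12.1.4.3 allows the RP2D to be the MTD, a lower dose or another dose. That stands. It limits the damage to the choice of RP2D, but not to the report on the primary objective.

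**Conclusion.** The point holds in two limited parts. First, the 8.3 criterion and the DLT rule can give conflicting safety statements when a tolerated DLT is also serious, and neither 8.3 nor 14.3.5 says which governs. The chance of this is 0.20 to 0.50 for a DLT risk of 1% to 5% if every DLT is serious, and 0.16 at 5% if a quarter are. These figures rest on an assumed common risk, an assumed serious share and a clean cohort 1. Second, section 8.2.2 rules out an outcome that 12.1.4.3 provides for, in the branch the protocol itself makes likely. What can be concluded about safety and the top dose depends on resolving both.

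**What to change.** Reconcile sections 8.2.2, 8.3, 12.1.4.2, 12.1.4.3 and 14.3.5:

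- State whether the 8.3 criterion or the DLT rule governs the safety conclusion, and over which dose levels and time window.
- Use one meaning of MTD throughout, including the definition in 8.2.2 and its level 5 sentence. Changing only one of these would leave a new contradiction. The report should make clear whether a toxicity limit was found or only that the highest tested regimen was tolerated.
- Report severe related SAEs by dose level with exact confidence intervals.

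No dose, escalation or stopping rule is proposed here; which reading is intended is for the sponsor to settle. The cost is a few sentences of protocol text. The claim at the top dose may become more modest.

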#### **8.3.1 Primary endpoint: MaaT033 tolerability**

Occurrence of MaaT033 limiting toxicity-related treatment emergent (serious) adverse events, grade $\geq$ 3, from treatment start (visit 1) to the next cycle (visit 3). AE and SAE relationship will be validated by a final safety committee. Cf safety description § section 12. All adverse events will be categorized according to the CTCAE v5.0 criteria.

Tolerability assessment will be done with the evaluation of LTD. Based on the MTD and MAD evaluated in the different cohorts, the best dose regimen in terms of activity might be re-evaluated. Therefore, the minimal dose that is safe and active will support the best dose regimen that may need to be adjusted correspondingly.

#### **8.3.2 Secondary endpoint: Dose regimen evaluation**

MaaT033 best dose regimen will be evaluated based on different evaluations:

- Overall safety will be evaluated from V1 to V4. All AEs will be evaluated by the safety committee.
- The product activity:

Definition of activity1 is here described by the evaluation of the microbiota modification: the proportion and number of different OTUs that colonize the gastro-intestinal tract of the patients. Assessment will be calculated using an alpha-diversity index (*i.e.* Richness, Shannon, Simpson or other ecology indexes).

Definition of activity2 is here described by the IMP bacterial engraftment: the percentage of bacteria that colonize the gastro-intestinal tract of the patients and come from MaaT033, as compared to baseline (visit1). Assessment will be calculated using Operational Taxonomic Units (OTUs) or a beta-diversity index (*i.e.* UniFrac, Jaccard, Bray-Curtis or other ecology indexes).

Activities1&2 will be assessed at V1, V2, V3 and V4.

- Patient compliance: Based on the level of compliance of the different cohorts evaluated with a daily follow up using a diary, the best dose regimen in terms of activity may be re-considered. For a patient, a compliance of less than 60% of capsules that were supposed to be ingested would not be considered acceptable to validate the corresponding dose regimen.

#### **8.3.3 Exploratory endpoints**

- Examination at, and evolution from V1 to V4, of the composition of the intestinal microbiota. Analysis includes but is not limited to the evaluation of the microbiota modification, based on diversity, and the richness index – using 16S and/or shotgun next generation sequencing (NGS) technology
- Examination of gut inflammation markers (stool, blood), immuno-monitoring
- Based on molecular analyses, description of gut resistome carriage from V1 to V4.

|                                                                                   |                    |                                                                      |
|-----------------------------------------------------------------------------------|--------------------|----------------------------------------------------------------------|
| [figure not shown] | DOCUMENT    | Protocol ID : MPOH05
EudraCT N° : 2019-004253-89
Version: 10.0 |
|                                                                                   | CIMON STUDY | Date : 04 MAY 2021
Page 26 / 70                                   |

## 9 **STUDY POPULATION**

### 9.1 **INCLUSION CRITERIA**

Each patient must sign and date the consent form prior to initiating any study-related procedures.

To be eligible for study participation, a subject must meet all the following criteria:

- 1 Male or Female
- 2 Age  $\geq$  18 years
- 3 Patients diagnosed with AML defined according to WHO 2016 criteria with  $\geq$ 20% leukemic blasts in the bone marrow or high-risk myelodysplastic syndrome, receiving intensive chemotherapy
- 4 Patients healthy enough to likely receive their consolidation or second cycle of chemotherapy after induction chemotherapy
- 5 Patients healthy enough to likely receive HSCT
- 6 Informed written consent
- 7 Patient recovered from neutropenia

### 9.2 **NON-INCLUSION CRITERIA**

Subjects are not eligible for study participation if they meet any of the following non-inclusion criteria:

- 1 Acute promyelocytic leukemia (AML-M3)
- 2 AML secondary to myeloproliferative disorder or chronic myelomonocytic leukemia (CMML)
- 3 Acute myeloid leukemia BCR-ABL1+
- 4 Active CNS leukemia
- 5 Patients with a life expectancy of <70 days according to investigator's opinion, or subject to therapeutic limitations
- 6 Confirmed or suspected intestinal ischemia
- 7 Confirmed or suspected toxic megacolon or gastrointestinal perforation
- 8 Active uncontrolled infection according to the attending physician
- 9 Any gastro-intestinal bleeding in the past 3 months
- 10 Any history of gastro-intestinal surgery in the past 3 months
- 11 Any history of inflammatory bowel disease
- 12 Any counter-indication to swallow capsules
- 13 Enrollment in another trial that may interfere with this study
- 14 Known allergy or intolerance to trehalose, maltodextrin or PEG
- 15 Women of childbearing potential without efficient contraceptive protection (appendix 2)
- 16 Pregnant or breastfeeding
- 17 Patients with EBV-negative serology
- 18 Subject who, in the judgment of the Investigator, is likely to be non-compliant or uncooperative during the study, or unable to cooperate because of a language problem, poor mental development;
- 19 Exclusion period of a previous study
- 20 Administrative or legal supervision
- 21 Confirmed positive result to SARS-CoV-2 test at screening

### 9.3 **NUMBER OF SUBJECTS PLANNED - REPLACEMENT POLICY**

The enrollment into the study will continue until a maximum of 27 subjects are treated with MaaT033 and evaluable, based on the step-up and safety process.

|                                                                                   |                    |                                                                      |
|-----------------------------------------------------------------------------------|--------------------|----------------------------------------------------------------------|
| [figure not shown] | DOCUMENT    | Protocol ID : MPOH05
EudraCT N° : 2019-004253-89
Version: 10.0 |
|                                                                                   | CIMON STUDY | Date : 04 MAY 2021
Page 27 / 70                                   |

If the compliance is under 60% for a patient, the patient will not be included in the evaluation of the dose-corresponding regimen but will be replaced by another patient.

If a patient becomes positive to SARS-CoV-2 (either nasopharyngeal, oropharyngeal swabs or salivary or other tests or feces tests) during the treatment period, it will be at the investigator's judgment to decide if the patient continues to take the capsules and stay in the study.

In case of COVID-19 pandemic in certain area of the country, an ongoing patient with unmonitored data can be considered to be replaced by another patient in another site in order to validate the corresponding dose regimen by the DSMB.

|                                                                                   |                    |                                                                      |
|-----------------------------------------------------------------------------------|--------------------|----------------------------------------------------------------------|
| [figure not shown] | DOCUMENT    | Protocol ID : MPOH05
EudraCT N° : 2019-004253-89
Version: 10.0 |
|                                                                                   | CIMON STUDY | Date : 04 MAY 2021
Page 28 / 70                                   |

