## 11.4 TERMINATION

### 11.4.1 Patient study withdrawal

Patients may be discontinued from the study in following situations:

1. Informed consent withdrawal by the patient or by the patient's legal representative;
2. Investigator's decision according but not exclusive to the following criteria:
  - Retroactive failure to fulfil inclusion/exclusion criteria;
  - Loss of contact, relocation. For lost to follow-up patients, investigator must make all possible attempts to reach the patient (phone calls, letters) with documented evidence.
  - New medical conditions not allowing for continuation of the protocol-conform treatment;

|                                                                                   |                    |                                                                      |
|-----------------------------------------------------------------------------------|--------------------|----------------------------------------------------------------------|
| [figure not shown] | DOCUMENT    | Protocol ID : MPOH05
EudraCT N° : 2019-004253-89
Version: 10.0 |
|                                                                                   | CIMON STUDY | Date : 04 MAY 2021
Page 41 / 70                                   |

- Occurrence of adverse events (such as allergic reactions to study drug, pregnancy, laboratory abnormalities) leading to substantial changes in the individual risk-benefit considerations that suggest a discontinuation of study drug
- 3. Any adverse event leading to interruption or contraindication of the MaaT033 treatment. Patients who stop treatment due to AE related to the procedure will continue to be monitored for safety follow-up. The reason for procedure stop must be documented (e.g., parenteral nutrition, impossibility to swallow).
- 4. Severe noncompliance to the protocol as judged by the investigator and/or MaaT Pharma.

In case of patient's withdrawal from the study, irrespective of the reason, an early study termination visit must be performed and recorded by the investigator in the appropriate forms of the eCRF and in the subject's medical records when considered as confirmed (e.g., date of and reason for withdrawal).

Subjects who have been withdrawn from the study cannot be re-included in the study.

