#### **12.1.4.2 Cohort Review Meetings:**

**Ad-hoc meetings can be called at any moment if needed for Safety consideration (DSMB).**

The dose-escalation process will be monitored by a **cohort review committee (DSMB, see corresponding chapter 8.2.2. for the dose escalation rules)**.

A cohort review meeting will be organized once all patients at a specific dose level have completed the V1 to V3 DLT period to decide regarding dose escalation. A cohort review meeting will also be organized as soon as DLTs are observed in 2 or more patients to decide about stopping the dose escalation and confirming the Maximum Tolerated Dose (MTD) has been reached:

Cohort1: 3 first patients in this cohort will allow the assessment of a potential unexpected safety signal and will confirm feasibility of the procedure. The CRC will review patients after treatment completion of the 3 patients. Safety, tolerability and DLT events between V1 and V2 will be evaluated to take the decision on dose escalation.

Cohorts 2&3: These cohorts present a more classical posology (daily treatment of 1 and 3 capsules respectively) in the microbiome capsule category (see section introduction). The CRC will review patient tolerability after treatment completion of the 6 patients of the evaluated cohort, completed with follow up information from of the previous cohorts. Tolerability and DLT events between V1 and V3 will be evaluated to take the decision on dose escalation.

Cohorts 4&5: No more dose regimen escalation are expected. Tolerability of those patients will of course be closely monitored. Because cohort4 will first be completed, a SC will validate the step up to cohort5.

The focus of this meeting will be to review the overall patients' safety and to ensure all DLTs have been identified to decide escalation to the next dose level, or to confirm if the MTD has been reached.

At the time of the decision to escalate the dose, the cohort review committee may recommend one or more of the following with the aim of establishing an MTD and/or enhancing potential safety and tolerability:

- That additional medication is used
- That specific measures are taken in the treatment of side effects based on AEs and building upon the cumulated experience in their management
- That caution is exercised in patients presenting with conditions that may exacerbate any observed toxicities

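### Section 9.3 replaces every patient under 60% compliance with no exception for a DLT, so a DLT that stops dosing early can drop out of the count of six used for escalation, MTD and RP2D

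*Protocol*

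**What the plan says.** **Replacement.** Section 9.3 states that under 60% compliance "the patient will not be included in the evaluation of the dose-corresponding regimen but will be replaced by another patient". The same section enrols until a maximum of "27 subjects are treated with MaaT033 and evaluable, based on the step-up and safety process". Section 8.3.2 sets the threshold per patient: "less than 60% of capsules that were supposed to be ingested would not be considered acceptable to validate the corresponding dose regimen".

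**Counting.** Section 8.2.2 defines the MTD as "Maximal dose for which only 0 or 1 patient do experience limiting toxicity out of a cohort of 6 patients". For cohorts 2 to 4, 0 or 1 DLT opens the next level; otherwise "If two or more patients out of 6 experiment a DLT, the study will be stopped". For cohort 5, "If one patient or less experiments a DLT, the MTD will be considered dose level 5"; with two or more, the MTD is level 4. Section 12.1.4.3 requires at least six patients and at most one DLT before a dose other than the MTD becomes the RP2D.

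**Toxicity can end dosing.** Section 11.4.1 lists among the grounds for withdrawal "Any adverse event leading to interruption or contraindication of the MaaT033 treatment". Section 11.4.2 adds a related life-threatening SAE, and section 11.4.3 makes treatment duration depend on tolerance.

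**Oversight.** Section 12.1.4 has the committee evaluate tolerability in every patient. Section 8.2.2 suspends inclusion and calls an ad hoc DSMB meeting if two or more patients have potential DLTs before the cohort is fully included. Section 12.1.4.2 calls a meeting "as soon as DLTs are observed in 2 or more patients to decide about stopping the dose escalation" and to confirm that the MTD has been reached. It also allows extra patients so that each cohort has enough who are evaluable for DLT, without defining evaluable.

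**The concern.** Low compliance can be a consequence of toxicity. A patient who stops capsules in the first days because of a DLT falls under 60%, and section 9.3, taken as written, removes and replaces that patient. A DLT that appears after most capsules have been taken stays in. The rule can therefore remove the earliest dose-stopping toxicities from the count it feeds.

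The decision turns on a single patient: 0 or 1 DLT continues, two or more stops. If one DLT patient is replaced and another is counted, the cohort may be read as 1 of 6 although two treated patients had a DLT. What should be a fixed stop then depends on which section the committee follows. The MTD definition and the RP2D condition are exposed in the same way.

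**Working it through.** **1. Sample size.** 3 patients in cohort 1 plus 4 × 6 in cohorts 2 to 5 gives 27, as stated in section 9.3. The same six patients per cohort serve both tolerability and activity (section 8.2.2).

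**2. When a stop triggers replacement.** Planned capsules (synopsis, dose regimen): 7, 21, 42 and 63 for cohorts 2, 3, 4 and 5. Compliance = capsules taken / capsules planned.

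- Cohorts 2, 3 and 5, stop after day 4: 4/7 = 12/21 = 36/63 = 57.1%, replaced. After day 5: 5/7 = 15/21 = 45/63 = 71.4%, kept.
- Cohort 4, stop after day 8: 24/42 = 57.1%, replaced. After day 9: 27/42 = 64.3%, kept.

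**3. The same cohort under each rule.** Seven patients treated, two with a DLT, one of whom stopped early.

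- Section 9.3 with the counts out of six: 1 of 6. The next level opens, or in cohort 5 the MTD may be read as level 5.
- All treated patients counted: two DLTs. The study stops in cohorts 2 to 4; in cohort 5 it stops with MTD = level 4.
- Two-DLT meetings: the committee decides. Neither meeting rule says whether the replaced patient is in the count.

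**4. Illustrative size.** The documents give neither a DLT rate p nor a share q of DLT patients who stop before 60%; both are assumed here. Patients without a DLT are taken as compliant, and both two-DLT meetings are ignored.

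- DLT rate among counted patients: r = p(1 − q)/(1 − pq).
- P(0 or 1 of 6) = (1 − r)^6 + 6r(1 − r)^5.
- Number replaced, N: negative binomial, six counted patients, success probability 1 − pq.
- P(0 or 1 counted, but two or more treated DLT patients) = P(0 counted)·P(N ≥ 2) + P(1 counted)·P(N ≥ 1).

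Worked case, p = 0.20 and q = 0.5: r = 0.10/0.90 = 0.111; P(0 counted) = 0.493; P(1 counted) = 0.370; sum 0.863. With 1 − pq = 0.90, P(N ≥ 1) = 0.469 and P(N ≥ 2) = 0.150. Result: 0.493 × 0.150 + 0.370 × 0.469 = 0.247.

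| True DLT rate p | P(0–1 of 6), every DLT counted | P(0–1 of 6), q = 0.5 | Reads 0–1 of 6 with two or more treated DLTs, q = 0.5 | Same, q from 0.25 to 0.75 |
|---|---|---|---|---|
| 5% | 96.7% | 99.1% | 2.9% | 1.6–3.9% |
| 10% | 88.6% | 96.4% | 9.6% | 5.1–13.1% |
| 20% | 65.5% | 86.3% | 24.7% | 12.2–35.9% |
| 1/3 | 35.1% | 65.5% | 34.8% | 15.2–57.8% |

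The figures for q = 0.5 are not upper bounds, because the result rises with q. Every cohort in the last two columns has two or more DLTs and so would also trigger the meeting in section 12.1.4.2.

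**The case against.** The strongest reply is that the 60% rule concerns activity. It appears under the secondary endpoint in section 8.3.2, where compliance may lead the best regimen for activity to be reconsidered, and neither the primary endpoint (8.3.1) nor the DLT definitions (8.2.2, 12.1.4.1) carry a compliance condition. Section 11.4.1 lists interruption for an adverse event separately from severe noncompliance and keeps patients who stop for a related event under safety follow-up. Capsules withheld for toxicity are arguably not capsules the patient was supposed to take.

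These readings are reasonable, and may be what was intended, but none is written. Section 8.3.2 places overall safety inside the dose-regimen evaluation, and section 9.3 ties evaluability to the step-up and safety process and regimen validation to the DSMB.

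A reader might infer that the protocol leads to a wrong escalation, or to an MTD of level 5. The documents do not support that. Section 12.1.4 evaluates every patient. The cohort 5 rule refers to two patients or more without a denominator, so two treated DLT patients meet it literally. Needing a replacement tends to keep inclusion open, so the suspension rule in 8.2.2 would often apply, and the meeting in 12.1.4.2 includes confirming the MTD. These safeguards stand, and they bring the case to the committee. They do not settle the count, and they leave to judgement what 8.2.2 makes automatic in cohorts 2 to 4.

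The size is also open to challenge. Section 12.1.4.1 expects no particular toxicity, section 6.4 reports 1 related SAE in 81 patients on the sponsor's enema products, and DLTs that arise after most capsules have been taken cannot trigger replacement.

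**Conclusion.** The gap is real. Section 9.3 is unconditional, toxicity can push a patient under 60%, and nothing says such a patient still counts among the six. This conflicts with the evaluation of every patient in section 12.1.4 and with the literal cohort 5 rule. A misreading needs at least two treated DLT patients in one cohort, at least one of them replaced. It is then a possible outcome of conflicting rules, not the path the protocol lays down.

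The percentages are illustrative: they rest on an assumed DLT rate and early-stop share and ignore the committee meetings. At the low toxicity the sponsor expects the effect is small (2.9% of cohorts at a 5% rate with half stopping early). It grows to 24.7% at 20%, in the range where a stopping rule matters most. The text should be corrected, because who is replaced and who counts are in-trial conduct rules, applied before any final analysis.

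**What to change.** Add to section 9.3, and refer to it from sections 8.2.2 and 12.1.4.2 so that it also defines who is evaluable for DLT:

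*A patient who took at least one capsule and has a DLT between V1 and V3 counts for escalation, MTD and RP2D whatever the compliance, and is not replaced for that purpose. Replacement for compliance under 60% applies only to patients without a DLT. An extra patient may be added for the activity assessment only.*

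The cost is protocol wording. At most one extra patient per early-stopped DLT is needed for activity, and the present text would already enrol that patient as a replacement.
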